### ***7.4 Stent implant***

The stent should be selected on the basis of the lesion length. The stent length must exceed the target lesion length by 5 mm (2,5 mm on each site). Direct stenting or pre-dilatation is at the discretion of the operator.

If multiple stents need to be implanted, the stent belongs to the same group as previously randomized.

Residual stenosis, after the stent implant, must be less than 30%. In those cases where the result is not optimal it is requested to postdilate the stent.

The implant procedure is considered successful if the residual stenosis is less than 30% with TIMI flow III.

If there are coronary dissections at the end of the stenting procedure, they must be treated with an additional stent from the same randomization group.

When stent implantation is not successful, cross-over to the other stent of this study or bare stent or balloon only, is allowed.

## **8. MEDICATION**

The medication guidelines, described in the protocol, should be preferably followed unless a different therapeutic treatment is necessary.

Pretreatment with ASA and clopidogrel is according to local protocol.

8 tablets of 75 mg clopidogrel should be given before angiography or as soon as possible in those patients who did not receive clopidogrel the day before.

Unfractionated heparin should be used at the beginning of the procedure. Target ACT 300 sec without abciximab or > 200 sec with concomitant use of abciximab.

ASA 80 mg or Ascal 100 mg (lifetime) together with clopidogrel 75 mg a day (**for 1 year !!**) is strongly advised. In case of clear indication for oral anticoagulants (OAC), this should be

combined with clopidogrel for 1 year. Also adding ASA for the first 2 weeks is advised. Less clear indication for OAC should be reconsidered and if possible and acceptable OAC should be stopped and changed into ASA and clopidogrel after the procedure.

## **9. FOLLOW-UP**

After discharge, patient follow-up will be performed after 30 days and 1,2,3 year by questionnaires. Repeat angiography will only be performed clinically driven by symptoms or signs of ischemia or when deemed necessary by the cardiologist. Information about in-hospital outcomes will be obtained from our institutional electronic clinical database and by review of the hospital records for those discharged to referring hospitals. Post-discharge survival status will be obtained from the Municipal Civil Registries at 1 month and 1, 2, 3 year. All repeat interventions (surgical and percutaneous) and re-hospitalizations will prospectively be collected during follow-up. Questionnaires regarding anginal status, intercurrent events and medication use will be discussed with all living patients by telephone at 12 months. Referring physicians and institutions will be contacted for additional information if required.

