### 5.1.1 Endpoint of the Study

The **primary endpoint** of the study is to assess the 12 month MACE (cardiac death, non-fatal MI, TVR) in all MCL PCI patients comparing the Xience stent to the CYPHER stent.

The **secondary endpoints** are:

- (Sub)-acute stent thrombosis (SAT) at 30 days and late stent thrombosis (LST) at 1, 2 and 3 year. (Definite and Probable, according to ARC definition). Possible stent thrombosis will be reported separately.
- Clinical MACE at 30 days and 2 and 3 years (cardiac death, non-fatal MI, TVR).
- All cause mortality at 1,2 and 3 year.
- Inability to deliver Cypher or Xience stent (cross over)

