#### Target vessel revascularization(TVR):

- TVR is defined as any repeat percutaneous intervention or by-pass grafting of the target vessel previously treated successfully with the stent.

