#### Major Adverse Cardiac Events (MACE):

- MACE is defined as any event during follow-up in hierarchical order: cardiac death, non-fatal re-infarction or TVR.

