### ***6.2 PREPROCEDURAL SCREENING.***

The patients are screened for inclusion and exclusion criteria before offering enrolment in the study. The patient should be informed on the study objectives and the required post procedure follow-up. The patient will provide witnessed oral consent before and sign the informed consent before or after the procedure.

Pre-procedure following is collected:

1. Demographic documentation
2. Clinical examination and clinical history
3. Blood analysis

The patient is considered enrolled in the trial when all selection criteria are met and the randomization envelop has been opened (**after the diagnostic angiogram**).

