### ***7.3 Randomization***

Randomization will be done by closed envelopes. The investigator chooses the envelope to the following sequential number available. The randomization code should be recorded on the CRF and notification form.

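### The TVR component of the primary endpoint does not exclude same-vessel procedures already planned at the index session, and no indication for repeat procedures is set to be recorded

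*Protocol*

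**What the plan says.** Section 5.1.2 gives the definition in full: "TVR is defined as any repeat percutaneous intervention or by-pass grafting of the target vessel previously treated successfully with the stent". The same section builds the composite on it: "MACE is defined as any event during follow-up in hierarchical order: cardiac death, non-fatal re-infarction or TVR". Section 5.1.1 makes that composite primary; the aim is to "assess the 12 month MACE (cardiac death, non-fatal MI, TVR) in all MCL PCI patients comparing the Xience stent to the CYPHER stent".

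Section 9 governs how patients come to repeat angiography: "Repeat angiography will only be performed clinically driven by symptoms or signs of ischemia or when deemed necessary by the cardiologist". It schedules no routine angiography. On data capture it says: "All repeat interventions (surgical and percutaneous) and re-hospitalizations will prospectively be collected during follow-up". It describes no classification of those interventions as planned or unplanned, or by indication.

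On knowledge of the stent, section 7.3 states "Randomization will be done by closed envelopes", and section 6.2 counts a patient as enrolled once the criteria are met and "the randomization envelop has been opened". Section 7.4 requires any further stent to come from the same randomised group, so the implanting operator knows the arm. The available text describes neither blinding nor blinded event adjudication. Part of the protocol just before section 4.2 is not available and could not be checked.

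**The concern.** A revascularisation component is meant to capture failure of the treated vessel after stenting. A second procedure on the same vessel that was already intended when the patient left the index session says nothing about how the stent performed, yet the word *any* in the definition takes it in. Such events add to both arms and pull the risk ratio towards 1.

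The second issue is discretion. Neither the definition nor the angiography rule requires ischaemia before a repeat procedure counts. If a clinician who knows the stent has a different threshold for the two devices, the primary endpoint moves for a reason unrelated to the device.

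The protocol itself fixes the definition, so this is not a detail left open for the SAP. A later SAP could also struggle to repair it: intent to stage is best recorded at the index procedure, and no field for it is described. The telephone discussion that covers anginal status is at 12 months, which may be long after a repeat procedure.

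**Working it through.** **1. What counts, reading the text literally**

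| Repeat procedure within 12 months | TVR under section 5.1.2? | Basis |
|---|---|---|
| Unplanned, on the stented vessel, with ischaemia | Yes | Definition |
| Unplanned, on the stented vessel, no ischaemia recorded | Yes | No ischaemia criterion; section 9 allows cardiologist discretion |
| Planned at index, on the same stented vessel | Yes, by inference | *Any* repeat procedure; the protocol never mentions staging |
| Planned at index, on a different vessel | No | Definition is limited to the target vessel |

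The third row is the defect. The second row is a choice that can be defended but cannot be examined unless the indication is recorded.

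**2. How much of the composite TVR might be**

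Simple ratios from section 2 (components can overlap):
- Bare stent, STEMI: 17.3 / 23.1 = 75%
- Sirolimus arm of the 712-patient randomised STEMI trial: 5.6 / 7.3 = 77% (denominator is target vessel failure, not MACE)
- Paclitaxel-stent STEMI registry: 6.6 / 14.7 = 45%
- Sirolimus-stent STEMI registry: 1.1 / 9.7 = 11%

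For drug-eluting stents the share runs from 11% to 77%.

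**3. Dilution (illustration)**

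There is no figure in the plan to reproduce: section 5.2.1 says that no sample size calculation was done. From the protocol: n = 1000 per arm; control rates 7.3% (target vessel failure), 9.7% and 14.7% (MACE), all from STEMI series. Assumed: two-sided 5%, risk ratio 0.7, and s points of non-device TVR added to both arms.

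With p1 = pc + s, p2 = 0.7·pc + s, d = p1 − p2 and p̄ = (p1 + p2)/2:
- SE0 = √(2·p̄(1 − p̄)/n)
- SE1 = √((p1(1 − p1) + p2(1 − p2))/n)
- Power = Φ((d − 1.96·SE0)/SE1)

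Worked case, pc = 9.7%, s = 0: d = 0.0291, p̄ = 0.08245, SE0 = 0.01230, SE1 = 0.01228. Then (0.0291 − 1.96 × 0.01230)/0.01228 ≈ 0.41, so power is 65.8%. With s = 3 points, d is unchanged, SE0 = 0.01413, SE1 = 0.01411, the ratio is 0.10 and power is 54.0%.

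| s (points, both arms) | Power, pc 7.3% | Power, pc 9.7% | Power, pc 14.7% | Observed RR at pc 9.7% |
|---|---|---|---|---|
| 0 | 52.8% | 65.8% | 84.7% | 0.70 |
| 1 | 47.4% | 61.3% | 82.3% | 0.73 |
| 2 | 43.0% | 57.4% | 80.0% | 0.75 |
| 3 | 39.5% | 54.0% | 77.8% | 0.77 |
| 5 | 34.2% | 48.4% | 73.8% | 0.80 |

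**4. Arm-dependent discretion (illustration)**

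True MACE equal in both arms, but one arm has b extra points of discretionary TVR. Same test, both tails counted, over the same three base rates (7.3% to 14.7%):

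| b | Extra events in one arm of 1000 | False-positive rate (nominal 5%) |
|---|---|---|
| 0.5 point | 5 | 6.1% to 7.1% |
| 1 point | 10 | 9.5% to 13.3% |
| 2 points | 20 | 23.3% to 36.7% |

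Neither s nor b has a source in the protocol.

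**The case against.** A pragmatic outcome study may reasonably count any TVR. Every drug-eluting-stent TVR rate cited in section 2 (1.1%, 7%, 5.6%, 6.6%) is given as plain TVR; only two pre-DES trials are described by ischaemic TVR. The absence of routine angiography already limits angiography-driven reintervention. Ischaemia fields completed by staff who know the stent would not remove bias. All of this stands, and it is why ischaemia-driven TVR belongs in a sensitivity analysis and not in the primary definition.

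Four stronger readings are tempting, and the protocol does not support them:
- *TVR counts every repeat procedure.* It does not. It is confined to the successfully stented target vessel, so staging of another vessel falls outside it.
- *TVR is the main driver of MACE here.* The sentence in section 2 that suggests this concerns primary PCI in STEMI and unplanned reinterventions. The cited DES shares, 11% to 77%, do not settle the matter for an all-comers comparison of two drug-eluting stents.
- *Repeat treatment is decided by clinicians who know the stent.* This is certain only for the implanting operator. Follow-up also runs through referring cardiologists and institutions, and whether they know the arm is not stated.
- *The primary comparison is biased.* Equal non-device events dilute without favouring an arm. Bias needs thresholds that differ by arm, and nothing in the text shows that they would.

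What the objection does not answer is the planned same-vessel procedure. No one would regard it as a stent failure, and the definition as written includes it.

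**Conclusion.** The point holds in a narrow form. The TVR definition lacks a rule for same-vessel procedures planned at the index session, and no indication is set to be recorded for repeat procedures, in a trial with no described blinding. Taken literally, planned same-vessel stages enter the primary endpoint as failures.

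The size is unknown because the protocol gives no rate for such events. Under the stated assumptions (9.7% control MACE, risk ratio 0.7, two-sided 5%, 1000 per arm), 1 to 5 added points cost about 4 to 17 points of power (65.8 − 61.3 = 4.5; 65.8 − 48.4 = 17.4). A 1-point arm difference in discretionary TVR would raise a 5% false-positive rate to between 9.5% and 13.3%. These figures show how sensitive the comparison is; they do not estimate what will happen. If same-vessel staging is rare at this centre, the effect is small. This is a cheap improvement and does not invalidate the endpoint.

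**What to change.** - In section 5.1.2, add to the TVR definition: *A target-vessel procedure declared as planned on the CRF at the end of the index procedure, and carried out without a new ischaemic event, is not counted as TVR.*
- For every repeat target-vessel procedure, record the indication on the CRF: symptoms, objective ischaemia or other.
- Keep MACE with any unplanned TVR as the primary endpoint, and pre-specify MACE with ischaemia-driven TVR as a sensitivity analysis beside it.

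This classifies endpoint events only and does not change when or whether a patient is treated. The cost is two CRF items, one sentence in the definition and a slightly lower event count. The events removed are planned procedures, so under the dilution model above their removal raises power. The indication field does not by itself protect against knowledge of the stent, but it lets a reader see whether discretionary procedures differ between the arms.

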## **10. ORGANIZATION AND MONITORING**

The clinical investigation plan requires that the investigator performs the clinical investigation on the patients as also the assessment of the patient's clinical status. The clinical follow-up will be performed before hospital discharge of the patient.

Patient data will be collected on Case Report Forms (CRFs). Data will be collected for the required study contacts according to the CRF Schedule. The Investigator will be required to sign each form to indicate the authenticity of the data submitted.

## **11. RISKS ASSOCIATED AND ADVERSE CLINICAL EVENTS.**

The potential risks related to this study are those typically reported for other coronary stents. These risks include, but are not limited to: possible occlusion of the stented vessel, death, myocardial infarction and need for target lesion revascularization, coronary artery perforation or dissection, peripheral bleeding, artery trauma at the

access site, stent embolization, cardiac arrhythmias due to drug side effects, hypersensitivity to the drugs or polymers on the stent.

### ***ADVERSE CLINICAL EVENTS***

Adverse clinical event means any unpredicted clinical complication, whether or not it is device related.

**Unpredicted adverse event:** any clinical event occurring to the patient, related to the device, not reported in the instructions for use.

**Severe adverse events:** any clinical event occurring to the patient, that is fatal, life-threatening, debilitating or results in prolongation of the hospitalization period. This includes but is not limited to: death, myocardial infarction, revascularization of the target vessel, severe bleeding.

All adverse events, unpredicted and severe, related to the device under evaluation must be reported by fax to the study monitor within 24 hours of their occurrence.

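### Section 11 defines adverse events inconsistently around the word *unpredicted*, so its 24-hour rule can be read as exempting expected severe device events

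*Protocol*

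**What the plan says.** The protocol's section 11 first lists the known risks of the procedure. They include "possible occlusion of the stented vessel, death, myocardial infarction and need for target lesion revascularization", and then perforation or dissection, peripheral bleeding, access-site trauma, stent embolization, arrhythmia and hypersensitivity.

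Under the subheading on adverse clinical events, four statements follow in this order:

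1. General term: "Adverse clinical event means any unpredicted clinical complication, whether or not it is device related".
2. Unpredicted adverse event: "any clinical event occurring to the patient, related to the device, not reported in the instructions for use".
3. Severe adverse events: "any clinical event occurring to the patient, that is fatal, life-threatening, debilitating or results in prolongation of the hospitalization period". Examples are given: "This includes but is not limited to: death, myocardial infarction, revascularization of the target vessel, severe bleeding".
4. Reporting: "All adverse events, unpredicted and severe, related to the device under evaluation must be reported by fax to the study monitor within 24 hours".

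The follow-up table in section 1 has an adverse-events row marked at every contact, from before the procedure to the yearly follow-ups.

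**The concern.** The general term should contain every subclass defined under it. Here it admits only complications that were not predicted, while the severe subclass names events that the same section has just listed as known risks. A reader who applies the general term literally would not count an expected complication as an adverse event at all.

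Two things are at stake. First, the fax to the study monitor is the only expedited safety report in the text at hand. Endpoint follow-up, at 30 days and at 1, 2 and 3 years, does not replace a prompt report. Section 14 says that both devices are already approved, so known complications should be among the contents of their instructions for use. If an event must be both severe and absent from those instructions, the rule could cover very little. Second, staff need one meaning of *adverse event* to fill in the adverse-events row in the same way for every patient.

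**Working it through.** No arithmetic applies, and the protocol states no figure on this point. The check sets the sentences against each other.

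**Step 1: the general term against the severe class.** The general term requires a complication to be unpredicted. The severe definition has no such condition and covers any clinical event that meets a severity criterion. Death and myocardial infarction stand in both the list of known risks and the list of severe examples. Bleeding also stands in both, as peripheral bleeding in the first and severe bleeding in the second. The risk list has target lesion revascularization and the severe list target vessel revascularization. If a listed risk counts as predicted, the subclass contains events that the general term excludes.

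**Step 2: the two senses of *unpredicted*.** In the general term, a relation to the device is expressly not needed. In the next definition it is needed, together with absence from the instructions for use. A complication unrelated to the device can therefore be unpredicted in the first sense and can never be so in the second.

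**Step 3: the reporting sentence.** It applies to device-related events. Within those there are four cases:

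| Device-related event | Unpredicted (second sense) | Severe | 24-hour report if the phrase names two categories | 24-hour report if both are required |
|---|---|---|---|---|
| Severe, not in instructions for use | yes | yes | yes | yes |
| Severe, in instructions for use | no | yes | yes | **no** |
| Not severe, not in instructions for use | yes | no | yes | **no** |
| Not severe, in instructions for use | no | no | no | no |

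The two readings give opposite duties in the second and third rows. The second matters most: it would hold a fatal, device-related stent occlusion if the instructions for use list occlusion.

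The sentence also opens by referring to adverse events. Correcting the conjunction alone would leave the second row open to dispute, because the literal general term still excludes expected events. Both sentences need the edit.

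**Step 4: what is collected regardless of section 11.** The composite in section 5.1.2 carries no condition of being unpredicted: "MACE is defined as any event during follow-up in hierarchical order: cardiac death, non-fatal re-infarction or TVR". Section 5.1.1 makes stent thrombosis (30 days; 1, 2 and 3 years) and all-cause mortality (1, 2 and 3 years) secondary endpoints. Section 9 takes survival status from civil registries and collects all repeat interventions and re-hospitalizations prospectively. What can fall out of the adverse-events row is therefore at most an expected complication that is neither severe nor an endpoint, for example non-severe access-site bleeding, a dissection or an arrhythmia.

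**The case against.** The best defence is that the protocol defines two categories and then names them. The phrase in the reporting sentence is set off by commas after a reference to all adverse events, so it most naturally lists the two classes. Requiring both would empty much of the severe definition. *Unpredicted* in the general term could also just mean unplanned in the individual patient; section 11 never says that a listed risk counts as predicted. This stands as the more natural reading. It does not remove the second reading, and it does not explain why one word has two senses in adjacent sentences.

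A second defence concerns collection. A reader might infer from the general term that stent occlusion, infarction, death and bleeding drop out of safety data. The documents do not support this. The endpoints and section 9 secure death, infarction, revascularization and stent thrombosis, and severe bleeding is named as a severe adverse event without further condition. The comparison of the arms rests on endpoint data, not on faxes. Section 9 also uses the hospital database and record review for in-hospital outcomes, and a 12-month questionnaire that covers intercurrent events. These may catch some of the remaining complications, and the case report form is not shown. This defence stands almost entirely, and it confines the collection gap to the residue in step 4.

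A reader might also put a number on the exempted events by applying the 1-year stent-thrombosis rates in section 2 to the whole trial: 2000 × 1.2% = 24 and 2000 × 3.4% = 68. That range is not supported:

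- Both rates come from patients with ST-elevation infarction, while this trial takes all comers.
- Section 2 notes that the 3.4% used a liberal definition. It also reports no angiographic thrombosis in 186 patients and 1% in a trial with a stricter definition.
- The figure 2000 counts both arms, whereas the rule speaks of the device under evaluation.
- How many events would be exempt depends on the instructions for use.

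**Conclusion.** The concern holds as an inconsistency of definition and an ambiguity of reporting. Section 11 limits adverse events to unpredicted complications, uses that word in two senses, and then names foreseeable events as severe adverse events. The 24-hour rule probably names two categories, but its wording allows the joint reading, which would exempt severe device-related events listed in the instructions for use. The trial's endpoints are untouched.

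The size cannot be expressed as an event count. The exemption rests on two assumptions: that a site adopts the joint reading, and that the event is listed in the instructions for use, which cannot be checked here. The collection gap further assumes that listed risks are treated as predicted and that the case report form does not ask for them separately.

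The change should be made, because the two readings give opposite duties for the same serious event. Independent capture of the endpoints keeps it from being critical. The restriction of the 24-hour rule to device-related events is a separate matter, not judged here.

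**What to change.** Reconcile the definitions in section 11 with three edits:

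1. Remove *unpredicted* from the general term, so that an adverse clinical event is any clinical complication, expected or not, and with or without a link to the device. Record all of these in the adverse-events row at each contact.
2. Keep *unpredicted* for one meaning only: a device-related event that is not in the instructions for use.
3. In the reporting sentence, replace *unpredicted and severe* with *unpredicted or severe*, so that an expected but severe device-related event is plainly included.

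Carry the same wording into the case report form instructions.

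The cost is some additional 24-hour reports and some additional case report form entries for expected, non-severe complications. If the site already reads the rule as naming two categories, edit 3 adds no reports. No visits or procedures are added.
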